## Abstract

Treatment adherence can improve the prognosis of severe mental illnesses. Self-report questionnaires are the main tools to measure it. However, a new assessment method has emerged: the electronic prescription system. This enables us to verify whether patients have collected their medication from the pharmacy, providing an objective measure of adherence. The ADHERA study aims to: (1) Compare digital self-report questionnaires with the electronic prescription system. (2) Identify factors associated with non-adherence. (3) Evaluate the effectiveness of an adherence-promoting intervention. This intervention will consist of the identification of patients with poor adherence and a subsequent program of psychoeducation led by clinical psychologists. Adherence will be reassessed six months later to evaluate the intervention’s effectiveness. By identifying key sociodemographic and clinical factors associated with non-adherence, this project will inform targeted interventions to support patients with schizophrenia and bipolar disorder. Furthermore, the psychoeducational telehealth program may represent an effective, scalable, and patient-centered strategy to improve long-term treatment adherence and clinical outcomes. If successful, this model could be implemented in other regions and chronic conditions, contributing to a more efficient and patient-focused healthcare system.

## 1. Introduction

### 1.1. Relevance and Impact of the Problem

Schizophrenia and bipolar disorder (BD) are severe mental health conditions affecting up to 1% and 2.4% of the global population, respectively (Merikangas et al., 2011; Marder & Cannon, 2019). Both disorders are characterized by disabling symptoms, including psychosis and mood dysregulation, and significantly impair patient functionality, caregiver well-being, and productivity. This creates a substantial economic burden, largely driven by indirect costs such as lost productivity, unemployment, and caregiver strain. For instance, BD is one of the top 10 leading causes of disability worldwide (Ferrari et al., 2016) and costs an estimated $45 billion annually in the US (Hirschfeld & Vornik, 2005), while schizophrenia incurs an even higher cost of $155.7 billion, with unemployment and caregiving-related productivity loss as major contributors (Cloutier et al., 2016). These financial burdens are exacerbated by high rates of treatment nonadherence, with more than half of affected patients experiencing it (Gibson et al., 2013). This non-adherence often stems from medication side effects, cognitive impairment, stigma, or a lack of insight into the illness (Haddad et al., 2014).

### 1.2. Treatment Adherence in Severe Mental Illness

Antipsychotic medication is one of the primary therapeutic tools in managing schizophrenia and bipolar disorders. Both conditions are chronic central nervous system disorders that impose a significant social and healthcare burden. It has been well established that treatment adherence substantially improves the prognosis of these illnesses (Loots et al., 2021). While non-adherence is a challenge across all mental health conditions, it is particularly critical in schizophrenia and bipolar disorder, where discontinuation rates reach 40–60% (Valenstein et al., 2006; Semahegn et al., 2020). In these disorders, medication adherence is the primary predictor of relapse and suicide risk, making them the priority focus for this digital monitoring protocol. Moreover, the clinical consequences of non-adherence in SCZ and BD, such as high rates of emergency re-hospitalization and neuroprogression (Berk, 2009), represent a disproportionate burden on the healthcare system (Pennington & McCrone, 2017).

Beyond psychosocial determinants, the promotion of adherence must be understood within contemporary pathophysiological frameworks. Emerging models suggest that the clinical stability provided by continuous pharmacological treatment is essential for maintaining neurobiological homeostasis. Specifically, stable treatment may protect the glymphatic system, which clears metabolic waste in the brain. As highlighted by Barlattani et al. (2025), disruptions in these clearance mechanisms and inflammatory processes are increasingly linked to relapse vulnerability in psychiatric disorders. Therefore, improving adherence in the ADHERA study may potentially not only stabilize behavior but also preserve critical neurobiological clearance systems.

Until relatively recently, the main methods available for measuring treatment adherence were self-report questionnaires, which could be administered either on paper or electronically via platforms such as the Patient Portal. This digital communication platform, operational in some hospitals, allows patients to access appointments and reports and to respond to online questionnaires known as PROMs (patient-reported outcome measures), including medication adherence surveys. A major limitation of these self-report tools is their susceptibility to bias: patients with poor adherence may claim they are taking their treatment when they are not, to avoid intervention from healthcare staff. Also, these questionnaires provide only a cross-sectional picture, whereas continuous long-term monitoring would be more accurate and useful. With the advent of digital electronic prescriptions (Roden et al., 2012), a novel approach to assessing adherence has emerged in several countries, including Spain. In the Community of Madrid, the Single Prescription Module (Módulo Único de Prescripción, MUP) provides access to the patient’s pharmacological history and enables prescription management on this platform. Additionally, this prescription system is interoperable with those of other Autonomous Communities across the country. The MUP allows verification that patients have collected their prescribed medications from the pharmacy, providing an objective method to assess treatment adherence. A critical distinction must be made between self-report adherence measures and dispensing-based data. While self-reports are cost-effective and provide insight into the reasons for non-adherence, they are frequently confounded by recall bias and social desirability, leading to an overestimation of compliance (Nguyen et al., 2014). In contrast, new dispensing data processing tools, such as the PRE2DUP-R package (Tanskanen et al., 2015; Vattulainen et al., 2025), provide an objective, longitudinal record of treatment acquisition. Although dispensing data does not guarantee the actual ingestion of the medication, it serves as a more reliable predictor of clinical relapse than subjective scales in severe mental illness and has been validated both in serum concentration and comprehensive drug treatment interview (Forsman et al., 2018; Krousel-Wood et al., 2015; Taipale et al., 2016).

Recent studies have further expanded the landscape of digital adherence monitoring. Randomized trials have demonstrated that digital medication systems can significantly improve adherence in community patients with severe mental disorders (Zhou et al., 2025). Scoping reviews have identified a growing evidence base for app-based and eHealth interventions targeting antipsychotic adherence in schizophrenia (Wu et al., 2023), although an international expert consensus has highlighted the ongoing need for validated standards and robust efficacy data in this field (Smith et al., 2024).

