### 2.3. Sample Size Calculation

According to our preliminary data, there are 5458 patients in our hospitals diagnosed with schizophrenia or bipolar disorder and with active antipsychotic dispensing registered in the MUP. Of these, an estimated 90% are registered on the Patient Portal, yielding an initial estimated sample of 4900 people.

Considering that completion of self-administered questionnaires on the Patient Portal is estimated to be around 30%, we expect an approximate sample of 1640 patients to perform the validation calculations for the adherence scales.

The sample size was calculated using G*Power (v3.1) for a one-sample means test (alpha = 0.05, power = 95%, effect size d = 0.5), yielding a minimum of 52 participants. This was based on previous studies exploring the ability of educational interventions to improve medication adherence in the medium term (Loots et al., 2021). Accounting for an anticipated dropout rate of up to 50%, the adjusted minimum is 104. We therefore set a recruitment target of 110 participants, well within the estimated pool of 656 patients expected to present with poor adherence.

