### 2.4. Procedure and Intervention

Project is expected to start in September 2026. We will access the MUP database and cross-reference it with data from the Patient Portal to identify our target sample, that is, those patients who received antipsychotic dispensations who also appear as active users of the Patient Portal. Within the entire sample, we will identify factors associated with adherence issues in the six months prior to the study. The entire sample will then be invited via a message through the Patient Portal to complete the self-report adherence questionnaires.

Finally, the subset of the sample identified with adherence problems will be the target sample for the intervention. Adherence problems to antipsychotics in people with schizophrenia or bipolar disorder are around 40–50%, although the variability in the studies is considerably high (Lingam & Scott, 2002). From the identified pool of patients with poor adherence, a recruitment target of 110 participants has been established. This sample size was determined using G*Power (v3.1) for a one-sample means test (alpha = 0.05, power = 95%, effect size d = 0.5), which requires a minimum of 52 participants (Loots et al., 2021). The final target of 110 accounts for an anticipated dropout rate of up to 50%, ensuring sufficient statistical power despite the high attrition typically observed in this clinical population.

The intervention program will be designed by clinical psychologists with experience in treating patients with bipolar disorder and schizophrenia after a review of the best protocols available in the literature. Presumably, participants will receive psychoeducational materials on the importance of adherence and the potential for mishap management. Tablet handling tips and medication-taking schedules will be reviewed. Participants will also be invited to a telehealth intervention comprising 10 online group psychotherapy sessions delivered via videoconference. These sessions will include cognitive-behavioral measures to manage adherence problems, and adherence will be monitored. Psychotherapy sessions will be led by clinical psychologists, and two sessions will feature testimonials from stabilized patients (See Figure 2).

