### 2.8. Statistical Analysis

Statistical analyses will be performed using R software version 4.5.3 and SPSS software version 30.0, or the latest versions available. All tests will be two-tailed, with 95% confidence intervals, and the level of statistical significance will be set at a *p*-value less than 0.05. The Morisky and Haynes scales (Morisky et al., 1986) will be measured prior to the intervention and again at the end of the sessions, and changes will be analyzed using Pearson’s correlation and simple regression. On the other hand, we will compare the total duration of antipsychotic exposure in the 6 months prior to the intervention with that in the 6 months following the intervention. Similarly, we will compare the average doses to which the sample was exposed before and after the intervention by calculating the recommended daily doses received.

To validate self-report questionnaires, sensitivity, specificity, positive predictive value, and negative predictive value will be calculated using medication collection data from the MUP as the gold standard. ROC curves will be constructed to determine the empirically optimal cut-off for classifying adherence, using the Youden index and reported with 95% confidence intervals, with PRE2DUP-derived antipsychotic exposure as the reference standard.

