To explore factors associated with higher or lower adherence, a logistic regression will be conducted, with adherence as the dependent variable. Adherence will be operationalized using the PRE2DUP method (Tanskanen et al., 2015; Taipale et al., 2016), generating two continuous outcomes: total duration of antipsychotic exposure (days) and average daily dose in DDDs (Tanskanen et al., 2015). These continuous variables will be used as dependent variables in all regression analyses. Furthermore, linear correlations will be performed between adherence levels (using percentage of adherence as a continuous variable) and various potentially implicated factors. To identify factors independently associated with non-adherence, a multivariable logistic regression model will be constructed, incorporating sociodemographic and clinical variables as independent predictors and adjusting for potential confounders (age, sex, diagnosis, comorbidities, and urbanicity). Simple logistic regression and Pearson correlations will be conducted as preliminary exploratory analyses to inform variable selection for the multivariable model. Pre-post changes in adherence outcomes—including PRE2DUP-derived exposure duration and average daily dose in DDDs, as well as self-report scale scores—will be analyzed using linear mixed-effects models, with time (pre- vs. post-intervention) as a fixed effect and subject as a random effect, adjusting for diagnosis, age, and sex.

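### The pre-post change in the self-report scales can reflect a change in reporting as well as in adherence, and the single pre-intervention validation does not rule this out

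*Protocol article*

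**What the plan says.** Section 1.2 of the protocol article describes how self-report goes wrong. Poor adherers have a motive to conceal: "patients with poor adherence may claim they are taking their treatment when they are not, to avoid intervention from healthcare staff". More generally, of self-reports, "they are frequently confounded by recall bias and social desirability, leading to an overestimation of compliance".

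Section 2.4 places the questionnaire survey before the intervention: "The entire sample will then be invited via a message through the Patient Portal to complete the self-report adherence questionnaires". Section 2.3 gives the size of that survey: "we expect an approximate sample of 1640 patients to perform the validation calculations for the adherence scales". The validation in section 2.8 is of these responses: "sensitivity, specificity, positive predictive value, and negative predictive value will be calculated using medication collection data from the MUP as the gold standard". No second validation is described.

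The poorly adherent subset is then offered ten online group sessions led by clinical psychologists. Section 2.4 says of them: "These sessions will include cognitive-behavioral measures to manage adherence problems, and adherence will be monitored". In section 2.8 the scales "will be measured prior to the intervention and again at the end of the sessions", and the pre-post outcomes include exposure and dose "as well as self-report scale scores—will be analyzed using linear mixed-effects models". Section 2.1 makes this a single-arm comparison with each participant's own baseline.

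On which measure leads, section 2.5 says the main outcome is measured by the Morisky-Green scale and the Haynes-Sackett question, and adds MUP exposure as a measure of effectiveness. Section 4.3 calls dispensing data the primary outcome.

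**The concern.** By the protocol's own account, the error in the scales depends on how the respondent stands towards the clinical team. The intervention changes that relation between the two measurements. Sessions that promote and monitor adherence could make participants keener to report good adherence. The deliberately non-coercive approach described in section 1.4 could instead make them more candid. Either way, the reporting error need not be the same before and after, and with one arm there is no control group to absorb the difference.

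Sensitivity and specificity estimated in the Portal survey describe reporting before the psychoeducation. They do not show how the same people report at the end of it. A scale improvement may therefore be partly or wholly a reporting change, and a real gain may be hidden by greater candour. Hypothesis 1 in section 1.6 says only that adherence will increase, and no rule is given for the case where scales and dispensing disagree.

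**Working it through.** **1. Does any stated analysis separate reporting from behaviour after the sessions?**
- The validation statistics and ROC curves in section 2.8 rest on the survey, which precedes the intervention.
- Section 2.8 also mentions Pearson's correlation and simple regression for the scale changes, but does not say what they are to be correlated with or regressed on.
- The mixed models in section 2.8 take scale scores, exposure duration and average dose as outcomes, with time as a fixed effect. No model or agreement analysis is stated that links scales to exposure after the sessions.
- The limitations in section 4.3 cover Portal selection, dispensing as a proxy, attrition and MUP coverage. They do not mention a change in reporting.

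**2. The plan's own sample size (section 2.3).** Inputs: one-sample test of means, alpha 0.05, power 95%, d = 0.5; two-sided by section 2.8.
- Normal approximation: n = ((1.960 + 1.645)/0.5)² = 51.98, so 52. The stated figure is reproduced. The exact noncentral t gives 54, a difference of two.
- Dropout: 52/(1 − 0.5) = 104, as stated. The target of 110 leaves 110 × 0.5 = 55 completers.

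**3. What a pure reporting shift would do.** The documents give neither a size nor a direction, so the shifts below are assumptions. Let b be the mean reporting shift in SDs of the change score, with true change zero. The test statistic then follows a noncentral t with 54 degrees of freedom and noncentrality b × √55 = 7.416b, and rejection is at |t| > 2.005.

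| b (SD of change) | Noncentrality | Probability of a significant result |
|---|---|---|
| 0 | 0 | 5% (2.5% in the favourable direction) |
| 0.1 | 0.74 | 11% |
| 0.2 | 1.48 | 31% |
| 0.3 | 2.22 | 59% |
| 0.5 | 3.71 | 95% |

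From b = 0.1 upwards almost all of this is in the favourable direction. The table uses the one-sample test of the sample size calculation. With complete pairs and covariates fixed over time, the test of time in a random-intercept model comes to the same comparison.

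**4. The opposite direction.** If the true change is d = 0.5 and candour offsets it by 0.3 SD, the visible change is 0.5 − 0.3 = 0.2 SD. By the table, it is detected in about 31% of trials, against about 95% without the offset.

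**The case against.** The best defence is that the design already answers most of this. Section 1.2 states the bias as a reason to prefer dispensing data. Section 2.5 links MUP exposure to measuring effectiveness, section 4.3 calls dispensing primary, and section 2.8 compares exposure over six months before and after. That comparison does not depend on what patients say. This stands, and it confines the point to the scale results.

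A reader might infer that reporting change and adherence change cannot be told apart at all. The documents do not support that: both changes will be reported for the same people, so a scale gain without a dispensing gain would be visible. What is absent is a joint analysis and a rule for reading discordant results.

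A reader might also infer that Hypothesis 1 would be declared met on the scales alone. No section sets such a rule. No section excludes it either, because section 2.5 gives the main outcome to the scales while section 4.3 gives it to dispensing.

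The size is assumed, and the 95% at 0.5 SD only restates the planned power for an effect of that size. The section 2.4 paragraph on the programme is itself provisional, and it does not say who does the monitoring; that staff do so is inferred from sessions led by psychologists.

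Finally, an article may leave a joint analysis to a fuller document. But this article itself states the bias, gives the scales the main outcome, sets out their pre-post analysis and contradicts itself on which measure leads.

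**Conclusion.** The point holds for the self-report outcomes. As written, the plan can credit a reporting shift to the intervention, or lose a real gain to candour, and the single pre-intervention validation does not protect against this. It matters most if section 2.5 governs and less if section 4.3 does.

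The sizes (11%, 31%, 59% and 95% for shifts of 0.1, 0.2, 0.3 and 0.5 SD) assume 55 completers, zero true change and a shift that the documents do not quantify. They show sensitivity to a shift; they are not an estimate of what will happen. The direction is equally open.

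Two further readings go too far. The effectiveness evaluation as a whole is not undermined, since the MUP comparison is unaffected by candour. Nor were the scales validated in untreated people: section 2.2 requires an active antipsychotic prescription, so the validation sample is only prior to the psychoeducation.

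**What to change.** 1. Reconcile sections 2.5 and 4.3 so that the pre-post change in PRE2DUP-derived exposure decides the effectiveness conclusion for Hypothesis 1, and scale change is supportive only.

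2. In section 2.8, add a within-person comparison of self-report with continuous percentage exposure, before and after, in all intervention participants who have both measures. Put the two on a common metric, for example by standardising each to its baseline SD, and report the change in the discrepancy with a 95% CI. Align each MUP window with the period the scale refers to: the scales are repeated at the end of the sessions, whereas the planned MUP window is the six months after the intervention. Do not restrict the comparison to those who are poor adherers by MUP at each time. That would change the denominator, condition on post-intervention status and need a cut-off the protocol does not state.

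3. State that a scale improvement without a supporting estimate and CI for the change in MUP exposure will be reported as not confirmed by dispensing, and not as evidence of effectiveness. Movement in the same direction alone is not enough: in a sample selected for poor adherence, MUP exposure may rise by regression to the mean. The same statement should note that MUP does not confirm ingestion, so discordance is not proof of misreporting.

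The cost is one analysis on data already planned, a few sentences and a more cautious reading of the self-report result. Precision is limited: with 55 pairs, the 95% CI for the mean change in discrepancy has a half-width of 2.005/√55 = 0.27 SD of that change, so a small shift in reporting could be missed.

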### 1.3. Previous Literature and Rationale

Numerous studies have explored the concept of treatment adherence in schizophrenia (Acosta et al., 2012). For instance, the study by Kim et al. (2020) examined adherence and illness insight within the context of the CATIE antipsychotic treatment clinical trial. They found that impaired insight into the illness was a key predictor of earlier nonadherence to antipsychotic medication, underscoring the importance of interventions aimed at improving illness awareness to support long-term treatment adherence in schizophrenia.

Treatment adherence in BD has been widely studied; however, its critical determinants remain uncertain, as demographic and illness-related factors have consistently failed to fully account for or predict non-adherence (Chakrabarti, 2016). The latter suggested a patient-centered approach, highlighting the influence of attitudes toward medication, therapeutic relationships, stigma, and access to care—factors that may better explain non-adherence and guide more effective interventions. Additionally, psychological traits such as affective temperaments are increasingly recognized as relevant factors in adherence. Depressive temperaments have been associated with lower medication adherence, although self-care abilities may mitigate this association (Visalli et al., 2024), supporting the need for personalized strategies.

However, due to the relatively recent implementation and widespread adoption of electronic prescribing modules in many countries, fewer studies have utilized this method to assess treatment adherence.

